Disability associated with hospitalization (DAH): Hospitalization often impairs the functional capacity of elderly individuals, especially the frailest ones (3-6). This DAH is due to multiple barriers to mobility during hospitalization related to the patient (disease, comorbidities, etc.), treatment (rest, procedures, medications, etc.), the institution (availability of personnel, assistive equipment, etc.), and the attitudes of the patient and staff (7). A recent study demonstrates that beyond individual risk factors, one of the main factors associated with DAH at discharge and 1 month later is low mobility during hospitalization (5). Ten days of bed rest cause a significant loss of total lean mass and strength in the lower limbs (8, 9). Muscle strength loss can be as high as 5% per day, so ten days of hospitalization can lead to a 50% loss of strength (5). Furthermore, the consequences of inactivity are more severe in the elderly compared to younger individuals (10). DAH is highly prevalent: between 40-50% of hospitalized elderly individuals, even for a short period of time, experience a decline in their functional capacity at the time of discharge (11-14). The progression of this decline once the acute illness that led to hospitalization has resolved is highly variable: between 30 and 60% of elderly individuals who experienced disability during the hospitalization recover it some time after discharge (15). Data collected in our acute care unit show that 389 out of 627 patients (62%) are discharged with DAH (data being prepared for publication). The consequences of disability are devastating for the patient and the healthcare system (5). Many patients who are discharged with new disabilities and do not recover are unable to live alone, requiring supervision at home or institutionalization into a residential facility. Additionally, DAH is associated with poor hospital outcomes: longer stays, increased complications, and increased mortality. Thus, elderly individuals who experience less functional deterioration during hospitalization have a 10.7% three-month mortality rate, compared to 36.7% for those who experience the greatest functional deterioration (16). Data from our service indicate an increase in mortality at 6 and 12 months for patients discharged with DAH, compared to patients who did not experience deterioration or recovered their functional status at discharge (data being prepared for publication). Typically, hospital stays do not promote mobility in the elderly. Between 73 and 83% of the time an elderly individual is hospitalized, they are usually bedridden (17, 18). Even very short hospital stays can involve bed rest and low levels of activity, which are associated with negative functional outcomes (6). Compared to patients with higher levels of activity during hospitalization, those with bed rest or low levels of any type of activity (physical therapy, independent or assisted activity) had higher rates of DAH and a greater risk of institutionalization and death at discharge and thirty days post-discharge (6, 19). This relationship between low mobility levels and functional decline remains significant after adjusting for multiple variables and cofactors, such as

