### 112        **4. DESIGN**

113        Randomized clinical trial designed according to the Consolidated Standards of Reporting Trials statement  
 114        (CONSORT) recommendations (Altman DG, Ann Intern Med 2001; 134:663-694). After signing  
 115        informed consent, subjects will be randomly assigned, in blocks of four weeks, to the intervention group  
 116        (IG) or the control group (CG). The IG will undergo the physical training and health education program,  
 117        while the CG will receive standard hospital care. A follow-up phone call will be conducted at three  
 118        months after discharge to assess mortality, number of falls, and functional status. All tests (at admission  
 119        and at discharge) will be conducted in the same hospital unit by the same evaluators not involved in the  
 120        intervention. The study will be conducted following the Ethical Guidelines of the Helsinki Declaration.

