## SAMPLE SIZE

Calculated by estimating the proportion of patients who recover their baseline Katz index at 3 months post-hospital discharge. In our AGE CAR study, in the control group, 40% of patients recovered their baseline Katz index at 3 months. With the current intervention, we expect that 60% will recover the Katz index at 3 months. Therefore, with a statistical power ( $1-\beta$ ) of 80% and a significance level ( $\alpha$ ) of 0.05 (two-tailed), we need to analyze a total of 188 patients, rounded to the nearest "10," which is 190 patients. Hospital mortality in our unit is approximately 12%, and assuming a 20% loss to follow-up, we will need to include 252 patients, 126 in the intervention group and 126 in the control group.

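### On the plan's own allowances for death and loss, 252 inclusions leave about 177 analysable patients, not 190, and it is not stated whether the 20% covers deaths after discharge

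*Protocol*

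**What the plan says.** The trial is sized on the primary outcome: "Calculated by estimating the proportion of patients who recover their baseline Katz index at 3 months post-hospital discharge". The assumed rates come from AGECAR for control ("in the control group, 40% of patients recovered their baseline Katz index at 3 months") and from expectation for the intervention ("we expect that 60% will recover the Katz index at 3 months"). With 80% power and a significance level "of 0.05 (two-tailed), we need to analyze a total of 188 patients", rounded to 190. The step from analysable to included patients is a single sentence: "Hospital mortality in our unit is approximately 12%, and assuming a 20% loss to follow-up, we will need to include 252 patients", split 126 and 126.

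Two other places bear on that step. The Design section has a telephone call three "months after discharge to assess mortality, number of falls, and functional status", so deaths after discharge are foreseen. The Background cites a study in which elderly patients with less functional deterioration in hospital "have a 10.7% three-month mortality rate, compared to 36.7% for those who experience the greatest functional deterioration".

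**The concern.** The Sample Size section treats death as a reason for not being analysed, since it inflates the number for patients who die in hospital. The outcome is measured 3 months after discharge, so by the same logic a death in those 3 months also removes a patient. No term is named for it, and the text does not say whether the 20% is meant to include it.

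That raises two questions: whether 252 yields 190 on the two allowances that are stated, and how much lower the yield would be if deaths after discharge come on top. At stake is the stated 80% power. A null result would be read against that figure.

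**Working it through.** **Inputs** (Sample Size section): 40% v 60%; two-sided 5%; 80% power; 190 analysable; 12% hospital mortality; 20% loss to follow-up; 252 included, 1:1.

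**1. The required number.** Normal approximation with unpooled variance:

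n per arm = (1.96 + 0.8416)² × (0.4×0.6 + 0.6×0.4) / 0.20² = 94.2, or 188.4 in total.

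This reproduces 188. The pooled-variance formula gives 97 per arm (194 in total). Powers below are given as pooled / unpooled. At 190 they are 79.2% / 80.3%.

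**2. How 252 arises.** The protocol does not show the step. Multiplying up fits: 190 × (1 + 0.12 + 0.20) = 250.8, or 125.4 per arm, which rounds up to 126 per arm and 252. Compounding from 188 is also close: 188 × 1.12 × 1.20 = 252.7. Dividing by the retained fraction does not give 252:

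- losses in sequence: 190 / (0.88 × 0.80) = 269.9, so 270;
- losses summed: 190 / (1 − 0.32) = 279.4, so 280.

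Whatever the route, 190 of 252 is 75.4%, which allows for 24.6% attrition in total. The stated allowances amount to 29.6% in sequence (1 − 0.704) or 32% summed.

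**3. What 252 delivers on the stated allowances.**

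- Discharged alive: 252 × 0.88 = 221.8.
- With a 3-month Katz: 221.8 × 0.80 = 177.4. Power 76.4% / 77.6%.
- If 12% and 20% are both shares of those included: 252 × 0.68 = 171.4. Power 74.9% / 76.2%.

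The unpooled figure is Φ(0.20 / √(0.48/88.7) − 1.96) = Φ(0.76) = 77.6%.

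**4. Room left for losses after discharge.** 1 − 190/221.8 = 14.3%. All attrition after discharge, deaths included, must stay at or below this for 190 to be reached. The plan's own allowance is 20%.

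**5. If deaths after discharge are additional to the 20%.** Let d be mortality from discharge to 3 months. The documents give no value of d for this population.

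Analysable N = 252 × 0.88 × (1 − d) × 0.80

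| d | Analysable | Power (pooled / unpooled) | Inclusions needed for 190 |
|---|---|---|---|
| 0 | 177 | 76.4% / 77.6% | 270 |
| 10.7% (illustration) | 158 | 71.5% / 72.9% | 304 |

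The 10.7% is the lower of the two group rates in the cited study and serves only to show scale.

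**6. If deaths count as not recovered.** Only loss to follow-up then removes patients: 252 × 0.80 = 201.6 (taking the 20% of all included). If 40% and 60% already refer to all randomised patients, power is 81.5% / 82.6%. If they refer to survivors, hospital deaths alone dilute them to 0.88 × 40% = 35.2% and 0.88 × 60% = 52.8%, and power is about 71% (pooled).

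**The case against.** The strongest reply is that the 20% may already include deaths after discharge. Hospital death is named first and loss to follow-up second, which reads naturally as attrition before and after discharge. A caregiver may also answer the 3-month call, so a full 20% loss among survivors alone is not the obvious meaning. This stands: the absence of a separate death term is an ambiguity, not a proven gap. It does not rescue 190, because a 20% loss after discharge still leaves 177.

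A reader might also infer that the protocol puts this trial's post-discharge mortality at 10.7% to 36.7%, and so that power could fall below 60%. The documents do not support that. The two figures are groups of a cited study, separated by degree of functional deterioration. The protocol does not offer them as its own rate, and it does not say whether the three months run from admission or from discharge. The 36.7% belongs to the worst group and should not be used as an overall rate. The statement that 62% of the unit's patients leave with hospital-associated disability does not change this, since any such disability is not the same as the greatest deterioration. The eligibility criteria also exclude terminal illness and severe dementia.

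Nor is the fall from 190 to 177 caused by a missing death term. It comes from the inflation step. Only a fall below 177 could be put down to deaths outside the 20%.

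Finally, under intention-to-treat, deaths might count as non-recovery, which could bring power above 80%. How deaths are handled may properly sit in a SAP that is not shown, so its absence here is not a fault. But that reading fits poorly with a sample size that inflates for hospital deaths, and it helps only if the 40% and 60% are rates among all randomised patients, which the protocol does not say.

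**Conclusion.** The point holds in this form. On its two stated allowances, 252 inclusions give about 177 analysable patients and 76% to 78% power, not 190 and 80%. The power shortfall is modest, roughly 2 to 4 percentage points. It rests on deaths not being analysable, as the Sample Size section implies, and on the 20% applying to patients discharged alive; summing the two allowances gives 171.

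Whether the shortfall is larger depends on whether the 20% includes deaths after discharge, which is not stated. If it does not, the number is lower by an amount that the documents cannot fix; 158 patients and 72% to 73% power is an illustration, not an estimate. The requirement of 188, rounded to 190, is sound under the unpooled formula. All powers here take over the plan's own calculation, which treats patients as independent.

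**What to change.** In the Sample Size section:

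- Keep 188/190 as the analysable number required for 80% power.
- State what 252 delivers: about 177 analysable patients and 76% to 78% power, if the 20% includes deaths between discharge and 3 months.
- Say explicitly whether it does. If not, add a separate term for those deaths from AGECAR or the unit's own data, and lower the stated analysable number and power accordingly.
- If deaths are to count as non-recovery, put the 40% and 60% on the same all-randomised denominator before quoting power.

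The cost is a reworded paragraph and a less favourable stated power. No extra patients are required.

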## FAMILIARIZATION AND RELIABILITY ASSESSMENT

Before the study begins, all subjects will have familiarization sessions lasting about 30 minutes, consisting of an explanation of the study objectives and the performance of all tests. Test-retest reliability will be determined for each measurement of the primary variable in a subpopulation of subjects.

## ASSESSMENT OF ADVERSE EFFECTS (AEs)

Objectified or participant-reported AEs, including muscle pain, fatigue, and nonspecific pain, will be recorded by study personnel. Falls during the study period will also be assessed. An independent investigator will review all medical and nursing records to detect any falls.

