Balance: In a standing position, the patient will have to lift one knee for a certain period of time, progressing from 3 to 5 seconds. Subsequently, they will maintain balance by performing the same exercise with their eyes closed, following the same time progression. Up to 3 repetitions will be performed with each leg alternately. To stabilize the patient and provide safety, they will be held by the hands, while providing only necessary assistance.

Gait Stimulation: Patients who can walk with or without assistance will perform a gait stimulation exercise, which consists of walking as much as possible, with or without aid, for 10 minutes. The exercise will always be supervised, with the participant accompanied throughout the course. Participants should be able to maintain a conversation without difficulty breathing while walking. The time (up to a maximum of 10 minutes) and distance covered (according to marks placed in the hallway) will be recorded. When they are able to walk continuously for 10 minutes, the speed of movement will be increased.

Cool-down: Stretching exercises for major muscle groups will be performed, always adapted to individual characteristics of the participants.

Inspiratory Exercises: Participants will perform 30 inspirations through a device provided by the team (Power Breathe® Classic Medium Resistance) against 40% of maximum inspiratory pressure (PImax). Every 5 sessions, participants' PImax will be reassessed to adjust the workload.

Health Education: In each activity session, patients and caregivers will be taught how to perform the exercises to ensure they continue doing them at home, and prior to discharge, an entire session will be dedicated to reviewing the complete program. Essentially, the type, frequency, and progression of exercises to be performed will be reviewed. Participants will be explained how to perform them at home, and personalized written instructions with illustrations of the exercises will be provided. Additionally, one

month and two months after discharge, the professional who conducted the training will make a phone call to emphasize program adherence or address any doubts.

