### Measurement of Secondary Variables:

The Barthel Index assesses 10 items (feeding, bathing, dressing, grooming, bowel control, bladder control, toileting, transferring from bed to chair, ambulation, and stair climbing), with a range from 0 to 100 in 5-point intervals. A lower score indicates greater dependency (Mahoney F. Md Med J 1965; 14:61-65). The Functional Ambulation Classification (FAC) scale (Holden MK. Phys Ther 1984; 64:35-40) assesses walking ability in 6 levels: 0 unable to walk; 1 walks with substantial assistance from one person; 2 requires slight physical contact from one person; 3 walks independently but needs supervision from one person; 4 walks independently on level ground but cannot negotiate stairs; and 5 walks independently on level ground and stairs. These three scales (Katz, Barthel, and FAC) will be measured at 4 time points: 2 weeks before admission (baseline), at admission, at discharge, and at 3 months. The Short Physical Performance Battery (SPPB) (Guralnik JM. J Gerontol 1994; 49:M85-94) assesses the ability to perform three tasks (balance, gait speed, and chair stands) with a total score ranging from 0 to 12. Balance is evaluated by having the participant stand for ten seconds in three different positions: feet together, semi-tandem, and tandem. One point is awarded for each successfully performed position, with a range from 0 to 4. Gait speed is assessed by timing the participant walking 4 meters with or without the use of a cane or walker. Scores range from 4 (less than 4.8 seconds) to 0 (unable to perform). Chair stands measure the time it takes to stand up from a chair five times as quickly as possible without using the arms. Scores range from 4 (less than 11.2 seconds) to 0 (more than 60 seconds or unable to perform). These measures will be taken at admission and discharge. All outcome variables will be assessed by the same properly trained investigator who is not involved in the intervention. An investigator who did not participate in the training will conduct a telephone follow-up at three months post-discharge with the participant or caregiver (from both groups) to assess the functional status of ADLs (Katz index, Barthel index) and ambulation (FAC).

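### Patients are taught to keep exercising at home, but no post-discharge call is stated to ask about adverse effects other than falls and death, and only the intervention group gets the extra calls at which such effects might be volunteered

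*Protocol*

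**What the plan says.** **Home exercise.** Under Intervention Group, Health Education, the protocol says that at each session "patients and caregivers will be taught how to perform the exercises to ensure they continue doing them at home". A full review session before discharge and personalised written instructions follow. The Background (AGECAR Study) names this education as one of two changes from the earlier programme, the other being more exercise days in hospital.

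**Adverse effects.** The section on adverse effects says "Objectified or participant-reported AEs, including muscle pain, fatigue, and nonspecific pain, will be recorded by study personnel". It adds "Falls during the study period will also be assessed" and "An independent investigator will review all medical and nursing records to detect any falls". Falls have a stated period. The other effects have none.

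**Contacts after discharge.** There are three:
- Months 1 and 2, in the intervention group, at a first "month and two months after discharge, the professional who conducted the training will make a phone call to emphasize program adherence or address any doubts".
- Month 3, both groups: section 4 (Design) describes a call three "months after discharge to assess mortality, number of falls, and functional status".

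Measurement of Secondary Variables describes the month 3 call again, there as a call to "assess the functional status of ADLs (Katz index, Barthel index) and ambulation (FAC"), without naming mortality or falls.

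**The concern.** In hospital the trainer is present: walking is always accompanied, and patients are held by the hands during balance work. Daily session records also note why a session was not completed. A complaint of pain or fatigue can therefore reach study staff without a formal question. At home the protocol describes no study staff, so an adverse effect is recorded only if someone asks or the patient volunteers it.

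Two things are at stake. First, the tolerability of the home component, which is part of what is new in this trial, would be largely undocumented apart from falls and deaths. Second, any comparison of other post-discharge effects between groups would depend on how often each group is telephoned. An event that was never asked about cannot be recovered in the analysis, so this cannot be left to a statistical analysis plan.

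**Working it through.** The plan gives no figure to reproduce. The check sets the stated content of each post-discharge contact against the effects that the adverse-effects section lists.

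| Contact | Groups | Stated content | Falls or death | Muscle pain, fatigue, nonspecific pain | Injury |
|---|---|---|---|---|---|
| Month 1 call | Intervention only | Adherence, doubts | Not named | Not named | Not named |
| Month 2 call | Intervention only | Adherence, doubts | Not named | Not named | Not named |
| Month 3 call | Both | Mortality, number of falls, function (Design) | Named | Not named | Not named |

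1. The Data Source section lists interviews at admission and discharge and a telephone contact at 3 months. With the two calls under Health Education, that makes three scheduled contacts after discharge in the intervention group and one in the control group.
2. Contacts stated to ask about the listed non-fall effects: 0 of 3 in the intervention group and 0 of 1 in the control group.
3. The independent record review is directed at falls. It is not described as a search for other injuries, emergency visits or readmissions.
4. The adverse-effects section accepts participant-reported effects, so a complaint volunteered on any call could be recorded. Openings to volunteer are 3 against 1.

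The possible imbalance can be bounded under simple assumptions. Suppose the true event rate is the same in both groups, and that an event is volunteered with probability v at each later call, independently between calls. For an event soon after discharge:
- Intervention group: probability recorded = 1 − (1 − v)³ = 3v − 3v² + v³.
- Control group: probability recorded = v.
- Ratio = 3 − 3v + v².

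The ratio tends to 3 as v approaches 0 and equals 1 when v = 1. For an event between months 1 and 2 the intervention group has two later calls, and the ratio is [1 − (1 − v)²]/v = 2 − v. After month 2 it is 1. Under equal true rates, the apparent excess in the intervention group lies between none and threefold, and is largest for minor complaints that are seldom volunteered. The documents give no value for v, so this is a range and not an estimate.

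**The case against.** The strongest reply is that the protocol does follow harms after discharge. The month 3 call asks both groups about mortality and falls, two major harms for frail patients exercising at home. The adverse-effects section covers falls over the study period and backs this with an independent record review. It sets no cut-off at discharge for other effects, and study personnel speak to patients at every call, so nothing prevents recording them. The description under Measurement of Secondary Variables can be read as the functional part of the call and not its full content. No objective or hypothesis claims safety, and detailed event questions often sit in a case report form.

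Much of this stands, and it rules out several stronger readings:
- *Harms are monitored only in hospital.* The month 3 questions on falls and death contradict this, and the adverse-effects section leaves its period open without limiting it to the stay.
- *Post-discharge falls are lost.* This would require the caller to disregard both the Design section and the adverse-effects section. The two descriptions of the call differ in detail but are compatible.
- *Most of a three-month exercise period goes unmonitored.* No section gives the home programme a length. Setting AGECAR's median of three exercise days against calendar days at home would mix units, and that median is the very limitation this trial was changed to correct.

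What the reply does not meet is the narrower point. Permission to record an effect is not a plan to ask about it. The protocol says what each call is for, and the effects it lists are in none of them. The unequal number of calls is on the page whatever the case report form contains, and a safety claim is not needed for an adverse-effect comparison to mislead.

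**Conclusion.** The point holds in limited form. Non-fall, non-fatal adverse effects have no stated collection period and no scheduled post-discharge question, although intervention patients are expected to go on exercising at home. Followed as written, the plan does not elicit these effects in either group after discharge, and volunteered reports favour detection in the intervention group, with three calls against one.

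The conclusion rests on the stated content of the calls. If a case report form already asks both groups about these effects at month 3, the gap is one of wording, though the unequal calls at months 1 and 2 remain. Neither the primary endpoint nor the sample size is touched. This is an inexpensive improvement to data collection, not a flaw that threatens the main result.

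**What to change.** 1. Add to the existing month 3 call, in the same words for both groups, a short fixed set of questions on events since discharge: the effects already listed in the adverse-effects section, injury or fracture, and emergency visit or readmission.
2. Base any between-group comparison of post-discharge adverse effects on that call only. Report events volunteered at the month 1 and 2 calls separately, as intervention-group information.
3. State in the adverse-effects section that recording of effects and the independent record review run to 3 months after discharge.
4. Reword the description of the call under Measurement of Secondary Variables so that it names mortality and falls, as the Design section does.

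No extra visit, call or staff is needed. The cost is a slightly longer call and recall error for minor events, which the identical question set at least makes comparable in timing and wording between groups.

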#### 134        INTERVENTIONS

##### 135        Control Group (CG):

136        They will receive standard treatment, which includes protocols for delirium or functional decline  
 137        prevention, with removal of physical and pharmacological barriers and daily mobilization.

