##### 138        Intervention Group (IG):

They will receive physical training (PT) and health education. The PT program will consist of muscle strengthening exercises, balance training, gait stimulation, and inspiratory muscle training. The duration and intensity will be adjusted to the clinical situation and patient availability. Ideally, two PT sessions will be conducted daily (one in the morning and one in the afternoon), with an average duration of 30 minutes each, from Monday to Friday.

Warm-up: Each session will begin and end with a low-intensity warm-up and cool-down period of approximately 3 minutes, during which joint mobility exercises and stretching of major muscle groups will be performed.

Muscle Strengthening ("squats"): The muscle strengthening exercises will consist of a circuit primarily targeting the lower limbs (1-3 sets of 3-10 repetitions), alternating with exercises for the upper limbs (1-2 sets of 3-10 repetitions). They will be performed in a seated position on a chair with armrests, initially with both feet fully supported on the floor (knees flexed at 90°) and the back straight against the backrest (hip flexed at 90°). Starting from the initial position, participants will have to stand up from the chair and sit back down.

Difficulty Levels (not progressing to the next difficulty level until the patient completes 3 sets of 10 repetitions at the starting difficulty level):

1. With assistance, with arm support, without additional load, and with both feet supported.
2. With assistance, without arm support, without additional load, and with both feet supported.
3. Without assistance, without arm support, without additional load, and with both feet supported.
4. Without assistance, without arm support, with additional load, and with both feet supported (progress to the next difficulty level when reaching the maximum load allowed by weighted vests).
5. Without assistance, without arm support, without additional load, and with single-foot support.
6. Without assistance, without arm support, with additional load, and with single-foot support.

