## DATA SOURCE

Data will be obtained through interviews and review of medical records. Upon admission, each patient, family member or caregiver, and the responsible nurse will be interviewed. The patient and nurse will also be interviewed at hospital discharge, and a telephone contact will be made with the patient and family member or caregiver at 3 months post-discharge.

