## PARTICIPATION AND ADHERENCE

The expected benefits will be explained to participants in the intervention group to reduce dropouts and maintain good adherence to the program. The distribution of training sessions throughout the day will minimize fatigue and contribute to adherence. Adherence to training sessions will be monitored daily with specific records, as well as the reasons for non-completion of any sessions.

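### Symptom adverse effects have no common schedule, question or assessor, and intervention patients meet study personnel far more often, so a between-arm comparison of these symptoms would be confounded with ascertainment

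*Protocol*

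**What the plan says.** Only the protocol was available.

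- **Symptoms.** Assessment of Adverse Effects states: "Objectified or participant-reported AEs, including muscle pain, fatigue, and nonspecific pain, will be recorded by study personnel". It gives no schedule, question or assessor.
- **Falls.** The same section adds a second source: "An independent investigator will review all medical and nursing records to detect any falls". Under Design, the 3-month call also asks about falls.
- **Intervention-group contacts.** The Intervention Group section says: "Ideally, two PT sessions will be conducted daily (one in the morning and one in the afternoon"), Monday to Friday. Calls follow at one and two months after discharge, when "the professional who conducted the training will make a phone call to emphasize program adherence or address any doubts". Participation and Adherence adds daily session records, "as well as the reasons for non-completion of any sessions".
- **Control-group contacts.** The Control Group section says: "They will receive standard treatment, which includes protocols for delirium or functional decline" prevention. No study sessions and no calls at one or two months are described.
- **Contacts shared by both arms.** These are a familiarization session, the admission interview, the discharge interview ("The patient and nurse will also be interviewed at hospital discharge") and the 3-month call. Design lists mortality, falls and functional status as the content of that call; symptoms are not on the list. Under Design, the admission and discharge tests are done by evaluators outside the intervention. Under Measurement of Secondary Variables, an investigator who took no part in the training makes the 3-month call to both groups.

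**The concern.** Pain and fatigue are found mainly by asking, or by being present when the patient complains. If recording depends on contact with study personnel, and one arm has several times the contact, recorded counts can differ even when the true frequencies are equal. These symptoms are also plausible in acutely ill patients over 74 who never train, so the control group's rate is needed to judge what the programme adds.

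At stake is whether the trial can say that training does or does not cause pain and fatigue. The primary and secondary efficacy outcomes are untouched. The matter cannot be left to a statistical analysis plan, because symptoms that nobody asked about in the control group cannot be recovered by analysis.

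**Working it through.** The protocol gives no adverse-effect rate and no calculation for adverse effects, so there is no stated figure to reproduce. Its inputs are the planned 126 patients per arm (Sample Size), the contact schedules above, and the earlier AGECAR trial's median of three exercise days (Background). All symptom rates and capture rates below are assumptions.

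**Step 1: contacts per patient.** Count two sessions per training day, the two intervention-only calls, and three shared contacts (admission, discharge, 3 months). Familiarization is left out of both arms.

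| Training days | Intervention | Without the two calls | Control |
|---|---|---|---|
| 3 | 6 + 2 + 3 = 11 | 9 | 3 |
| 5 | 10 + 2 + 3 = 15 | 13 | 3 |

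These are upper counts, because two sessions a day is the ideal schedule.

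**Step 2: fixed capture rates.** Assume the same true rate in both arms, with 90% captured in the intervention group and 50% in the control group.

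- True rate 40%: 0.40 × 0.90 × 126 ≈ 45 and 0.40 × 0.50 × 126 ≈ 25. The pooled proportion is 70/252 = 0.278, SE = √(0.278 × 0.722 × 2/126) = 0.056, z = (0.357 − 0.198)/0.056 ≈ 2.8, two-sided p about 0.005.
- True rate 20%: 0.20 × 0.90 × 126 ≈ 23 and 0.20 × 0.50 × 126 ≈ 13. The pooled proportion is 36/252 = 0.143, SE = √(0.143 × 0.857 × 2/126) = 0.044, z = (0.183 − 0.103)/0.044 ≈ 1.8, p about 0.07.

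**Step 3: how far the result depends on capture.** Let π be the true rate, equal in both arms, q the chance that a contact reveals the symptom, and k the number of contacts after admission. Then P(recorded) = π × [1 − (1 − q)^k]. Take π = 0.30 and six sessions. The intervention group has k = 6 + 2 + 2 = 10, or 8 if the two calls collect no symptoms. The control group has k = 2. For q = 0.2 and k = 10: 0.30 × (1 − 0.8^10) = 0.268 against 0.30 × (1 − 0.8²) = 0.108, a ratio of 2.48.

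| q | Intervention (k = 10) | Control (k = 2) | Ratio | Ratio with k = 8 | Chance of a false significant difference, k = 10, 126 per arm |
|---|---|---|---|---|---|
| 0.1 | 0.195 | 0.057 | 3.43 | 0.570/0.190 = 3.00 | about 92% |
| 0.2 | 0.268 | 0.108 | 2.48 | 0.832/0.360 = 2.31 | about 91% |
| 0.4 | 0.298 | 0.192 | 1.55 | 0.983/0.640 = 1.54 | about 50% |
| 0.8 | 0.300 | 0.288 | 1.04 | 1.000/0.960 = 1.04 | about 4% |

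The ratios do not depend on π; the chances of false significance do. The model treats contacts as independent and the symptom as present at each of them, so it illustrates the range and does not predict a value. It shows two things: the bias can be large when contacts reveal symptoms only occasionally, and it almost disappears when the shared contacts reveal them reliably. Dropping the two calls changes little.

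**The case against.** **No symptom comparison is specified.** None of the objectives or listed outcomes is a symptom comparison, and Statistical Analysis gives only a general rule for comparing groups. The section may be meant to describe tolerability of the programme, for which intervention-group recording is informative alone. This stands in part: the point applies to a comparison if one is made. But the recording rule is not limited to one arm, a two-column descriptive table would carry the same bias, and an intervention-only listing has no comparator.

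**The control group may well be asked.** Participant-reported does not exclude active questioning, and the protocol is silent on whether the discharge interview covers symptoms. This also stands. The documents do not say that control patients are never asked; they only fail to ensure that they are asked equally.

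**Recording at the intervention-only calls is inferred.** Their stated purpose is adherence and doubts, and the session log is an adherence record. This is correct, but the sessions alone carry the point.

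**Stronger readings.** A reader might infer that every between-arm adverse-effect comparison is invalid. The documents do not support that, because falls have two sources covering both arms. A reader might also infer that any excess in the intervention group is pure artefact. That does not follow either: training can truly cause muscle pain or fatigue, and the trouble is that the design cannot separate the two.

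**Conclusion.** The point holds for symptom adverse effects. Ascertainment is not standardised across arms and opportunity to detect is unequal by design, so a comparison of recorded symptoms is confounded with ascertainment and likely biased towards more events in the intervention group.

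The size cannot be fixed from the protocol. Under the assumptions shown it runs from a recorded ratio of about 3.4 with weak capture per contact to 1.04 with reliable capture. Whether the difference reaches significance depends on the assumed rates: the 40% illustration does and the 20% illustration does not. The 126 per arm is also a ceiling; with the protocol's 12% hospital mortality, about 126 × 0.88 ≈ 111 per arm would reach discharge.

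This deserves correction because it concerns data collection, but it does not threaten the primary endpoint.

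**What to change.** In Assessment of Adverse Effects, state that evaluators not involved in the intervention ask every patient in both arms the same short symptom checklist at contacts that already exist:

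- at admission, as baseline only;
- at discharge, covering the hospital stay, as the main comparison;
- at the 3-month call, covering the time since discharge.

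Base any between-arm comparison of symptoms on these answers alone. Report events learned only in training sessions, session logs or the intervention-only calls in full, as a separate tolerability listing for the intervention group. Keep the record review for falls as it is.

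The cost is one short checklist and a few lines of text. Some transient symptoms linked to sessions will appear only in the descriptive listing, and these may be the ones most plausibly caused by training, so that listing should be shown beside the comparison. Recall at 3 months will be imperfect, which is why discharge should carry the main comparison. The checklist equalises the opportunity to report; it does not remove differences that arise because patients know their group.
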